**Effect of Sensory-Motor Exercises on Pain and Muscular Function:**

- Maryam Nazari Dehbazegi and colleagues in 2015 divided 53 patients with non-specific chronic low back pain into control and experimental groups. Sensory-motor exercises using a Huber device were performed for 5 weeks, with two 30-minute sessions per week. Significant improvements in lumbar movement control (Lomaguchi movement control tests) and pain reduction were observed in the sensory-motor exercise group compared to the control group (29).
- Michael A. McCaskey and colleagues in 2018 randomly assigned 22 patients with chronic low back pain to experimental and control groups. Both groups received routine physiotherapy for 30 minutes, but the experimental group also performed 15 minutes of sensory-motor postural exercises, while the control group performed 15 minutes of low-intensity cardiovascular exercises. Pain and function were assessed using the Oswestry Disability Index. Sensory-motor postural exercises had a significant impact on function but no significant effect on pain reduction or improvement in performance between the two groups with moderate pain (45).
- Jin Ah Hwang and colleagues in 2013 studied the effect of sensory-motor exercises on anticipatory postural control settings in chronic low back pain patients. Three groups were included: one group received conventional physiotherapy, another group received sensory-motor exercises, and the third group was a control group. The experimental groups performed their respective exercises for 40 minutes, 5 sessions per week for 4 weeks. Significant changes in pain, disability, and the onset of contraction in the transverse abdominal and external oblique muscles were observed. Sensory-motor exercises helped patients learn muscle control, resulting in reduced pain and improved function (46).
- Nisha Kanabar in 2016 examined pain and function changes using the Oswestry Disability Index. Patients were divided into two therapeutic groups: sensory-motor exercises (13 patients) and stability exercises (15 patients). Both groups performed exercises for 4 weeks, 5 sessions per week. Both types of exercises were effective in reducing pain and improving function in chronic non-specific low back pain patients, although sensory-motor exercises showed better effects (30).
- Benedict M. Wando and colleagues in 2011 conducted a preliminary study with three patients with chronic non-specific low back pain. The study aimed to evaluate the effectiveness of sensory-motor exercises combined with conventional physiotherapy. The results showed improved postural control, decreased pain, and increased lumbar flexion and extension, indicating the efficacy of sensory-motor exercises in combination with conventional physiotherapy (47).

This review highlights that the combination of tDCS and sensory-motor exercises shows promise in improving various outcomes, including pain, balance, and motor control. The effectiveness of these combined treatments varies across studies, and more research is needed to confirm their efficacy and establish optimal protocols for different patient populations.

**9. Study Type**

Randomized, single-blind clinical trial

**10. Study Population**

Target Population: Patients with chronic low back pain

Study Population: Patients with chronic low back pain who are accessible

**11. Sampling Method**

Samples will be selected through non-probability, voluntary sampling based on inclusion and exclusion criteria.

**12. Study Duration and Location**

From March 2022 to august 2023

Faculty of Rehabilitation, Tehran University of Medical Sciences – Biomechanics Laboratory and also the Brain Mapping Center of Iran

**13. Sample Size**

The sample size was calculated using G*Power 3.1.3 software, based on the Jafarzadeh et al. study [28], with pain as the primary outcome measure. The calculation used a between-group Cohen's f of 0.473, a power of 0.8, and an α of 0.05. This power analysis indicated that at least 30 participants were needed. To account for a potential 15% dropout rate, 34 participants were recruited.

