**17-2. Treatments**

After the initial assessment, individuals will be randomly assigned to one of two groups. The sequence will be generated using the website randomization.com with a balanced block randomization method. The block size will be 4. To ensure allocation concealment, sealed and numbered envelopes will be used, which will be provided to participants by the secretary. The treatment period for both groups will be 12 sessions, three times a week. After the treatment period, evaluations will be conducted again.

Due to the inclusion of a sham treatment, participants will be blinded, but blinding of the therapist or evaluator will not be possible.

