**18. Data Analysis Method**

- All descriptive and statistical analyses will be conducted using SPSS software version 23.
- Descriptive statistics will include the calculation of measures of central tendency (mean) and dispersion (standard deviation).
- The Shapiro-Wilk test will be used to assess the normal distribution of the data.
- To compare baseline (pre-treatment) between the two treatment groups, an Independent t-test with a significance level of 0.05 will be used.
- To examine the effects of within-subject factors (time stages: pre- and post-treatment) and between-subject factors (type of treatment: real transcranial electrical stimulation with sensory-motor exercises vs. sham transcranial electrical stimulation with sensory-motor exercises), a Two-Way Mixed between-within ANOVA will be employed. Effect sizes will be reported using η², and interpreted as small (0.01), medium (0.06), and large (0.14).
- Pearson Correlation will be used to assess the relationship between clinical parameters and neurophysiological parameters related to sensory and motor cortical excitability.

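### The 30 participants stated for 80% power are not tied to the planned group-by-time test, for which 30 gives about 56% to 90% depending on an unstated pre-post correlation

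*Protocol*

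**What the plan says.** Section 13 (Sample Size) reports a G*Power calculation based on an earlier trial, "with pain as the primary outcome measure". Its inputs are given in one sentence: "The calculation used a between-group Cohen's f of 0.473, a power of 0.8, and an α of 0.05". The result is "This power analysis indicated that at least 30 participants were needed", followed by "To account for a potential 15% dropout rate, 34 participants were recruited". The section does not give the test family, the sidedness, the number of measurements or the pre-post correlation, and it does not say what the 0.473 measures.

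Section 17-2 (Treatments) describes two groups, allocated by a "balanced block randomization method. The block size will be 4", so 30 evaluable patients means 15 per arm. Section 18 (Data Analysis Method) has a within-subject factor with two levels (before and after treatment) and a between-subject factor with two levels (real or sham stimulation, each with exercises), and states that "a Two-Way Mixed between-within ANOVA will be employed". It does not say which of the three effects in that model is the treatment test.

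**The concern.** In a randomised trial with one pre-treatment and one post-treatment score, a 2x2 mixed ANOVA offers three effects. The group main effect compares the arms on the average of the two scores. The time effect pools the arms. Only the group-by-time interaction asks whether the arms changed differently, and with two time points it is the same test as a t-test on change scores. That is the term that carries the treatment effect.

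The stated inputs do not give 30 for a plain two-sided comparison, so some unstated ingredient was used. If the stated power belongs to a different test from the one that will be interpreted, it says little about the trial's chance of detecting the effect. This matters here because Section 6 (Practical Implications) plans to read little difference between the groups as a sign that exercises alone suffice. That reading depends on the trial having the power it claims.

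**Working it through.** **Inputs from the protocol.** f = 0.473, so d = 2f = 0.946 for two groups; α = 0.05; power 0.80; N = 30 (Section 13). Two equal arms (Section 17-2). m = 2 measurements (Section 18). f² = 0.473² = 0.2237, so f²N = 6.712 at N = 30.

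**Assumptions, not in the protocol.** Pre-post correlation ρ, taken as 0.5 with a range of 0.3 to 0.7. For step 3, f is read as the post-treatment difference in single-time-point SD units. Tests are two-sided unless stated.

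Power is from the noncentral F distribution with noncentrality λ, or the noncentral t for the one-sided test.

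**1. Reproducing 30.** Three standard calculations give 30 as the smallest even N:

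| Calculation | Noncentrality at N = 30 | Power at 30 | Power at 28 |
|---|---|---|---|
| Repeated-measures ANOVA, between factors, λ = f²Nm/(1+(m−1)ρ), ρ = 0.5 | 6.712 × 2/1.5 = 8.95 | 82.3% | 79.4% |
| ANCOVA on the post score, λ = f²N/(1−ρ²), ρ = 0.5 | 6.712/0.75 = 8.95 | 82.2% | 79.3% |
| One-sided two-sample t, δ = d√(n/2), n = 15 per arm | 0.946 × √7.5 = 2.59 | 81.1% | 78.6% |

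The first fits the text best. It uses 0.473 as stated, matches the description of f as between-group, and uses the two measurements of Section 18. A one-sided test is stated nowhere, and the questions in Section 5 are non-directional. An ANCOVA is not planned.

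The between-factors match depends on ρ: that formula gives a minimum N of 26 at ρ = 0.3 and 32 at ρ = 0.6.

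**2. Calculations that do not give 30.**

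- Two-sided two-group comparison, λ = f²N, df 1 and N−2: 70.6% at N = 30. The minimum is N = 38, where λ = 0.2237 × 38 = 8.50 and power is 81.0%.
- G*Power within-between interaction with f entered as the interaction effect, λ = f²Nm/(1−ρ), ρ = 0.5: minimum N = 12, and 99.9% at 30. The stated 30 is therefore not the minimum for the interaction under that convention either.

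**3. Power of the group-by-time test.** The arms are taken to differ only after treatment, by 0.946 SD. The change score has variance 2(1−ρ) in squared-SD units, so λ = f²N/(2(1−ρ)), df 1 and N−2. For the baseline-adjusted ANCOVA, λ = f²N/(1−ρ²), df 1 and N−3.

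| ρ | λ, group-by-time, N = 30 | Power, N = 30 | Power, N = 34 | N for 80% | ANCOVA power, N = 30 |
|---|---|---|---|---|---|
| 0.3 | 6.712/1.4 = 4.79 | 56% | 62% | 52 | 74% |
| 0.5 | 6.712/1.0 = 6.71 | 71% | 76% | 38 | 82% |
| 0.6 | 6.712/0.8 = 8.39 | 80% | 85% | 32 | 88% |
| 0.7 | 6.712/0.6 = 11.19 | 90% | 93% | 24 | 94% |

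At ρ = 0.5 the change-score variance equals the single-score variance, which is why 71% and 38 reappear from step 2. The N = 34 column assumes no loss; with the protocol's own 15% dropout, 34 × 0.85 = 28.9 remain.

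**The case against.** The strongest reply is that the routine behind 30 is not stated and can only be inferred. Three calculations give 30, and one of them, the ANCOVA, would be a sound test of treatment. A reader might infer that the authors demonstrably sized the trial on the averaged group main effect. The protocol does not support that: it is the most plausible source, not the only one, and the match needs a correlation of 0.5 that the protocol never mentions.

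A reader might also infer that the trial simply has 71% power. That figure needs ρ = 0.5 and one particular reading of f. At ρ = 0.6 the group-by-time test reaches 80%, and at 0.7 it reaches 90%. If 0.473 were G*Power's interaction effect, 30 patients would be more than enough, although 30 would then not be the minimum.

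A third tempting inference is that the averaged main effect will be read as the treatment test. If the arms differ by 0.946 SD only after treatment, averaging halves the difference: λ = (f/2)² × 30 × 2/(1+ρ) = 2.24 at ρ = 0.5, and power is 30% (34% at ρ = 0.3, 27% at 0.7). No section says this effect will be used for inference, and the planned model contains the group-by-time term, so these figures are not the trial's power.

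All of this stands as a limit on the claim. It does not remove the point: on none of the three routes does 30 come from the group-by-time test, and the protocol gives no basis for attaching 80% to it.

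**Conclusion.** The point holds in limited form. The sample-size statement cannot be reproduced from its stated inputs as a two-sided two-group comparison, which needs 38. Every route found to 30 adds something unstated and leads to a test other than the group-by-time term of the planned ANOVA. Reading f as the post-treatment difference in single-time-point SDs, 30 patients give that term 56% to 90% power over correlations 0.3 to 0.7, and it reaches about 80% only from a correlation of about 0.6. The stated 80% is therefore not assured for the planned test. It is not shown to be wrong at every plausible correlation.

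The flaw concerns the claimed power and the link between Sections 13 and 18. It biases no estimate or p-value, but it weakens the conclusion Section 6 would draw from a small difference between groups.

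**What to change.** Both sections need editing, so that the powered test and the planned test agree.

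- **Section 13:** name the test being powered, its sidedness, the assumed pre-post correlation and what f = 0.473 measures. Restate power at 30 evaluable patients as a range over correlations.
- **Section 18, preferred:** make the treatment test for pain the post-treatment between-group difference adjusted for baseline pain (ANCOVA). On the reading of f used above, 30 patients give 74%, 82% and 94% at correlations 0.3, 0.5 and 0.7. The baseline score is already collected.
- **Section 18, alternative:** keep the mixed ANOVA, name group-by-time as the treatment test, and quote its lower power (56%, 71% and 90% at the same correlations).

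The cost is a paragraph in Section 13 and a sentence or two in Section 18. The enrolled number need not change. The drawback is a less favourable stated power at low correlation: at 0.3 even the ANCOVA falls short of 80%, and the protocol should say so.

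### Recruiting 34 allows for 11.8% dropout, not the stated 15%: at 15% about 29 complete, one to two short of the protocol's own minimum of 30 (minor)

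*Protocol*

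**What the plan says.** Protocol section 13 (Sample Size) bases the calculation on pain, with a between-group Cohen's "f of 0.473, a power of 0.8, and an α of 0.05". It reports that "at least 30 participants were needed" and continues: "To account for a potential 15% dropout rate, 34 participants were recruited". It does not give the formula used to get from 30 to 34, the G*Power test chosen, or a correlation between the two measurements.

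Section 17-2 (Treatments) describes two groups, randomised "with a balanced block randomization method. The block size will be 4", so the arms are meant to be equal. No other section gives a different dropout rate or recruitment number.

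**The concern.** A dropout allowance is meant to leave the required number of participants after the expected losses. Here the required number, the dropout rate and the recruited total all stand in one short paragraph, and the total is too small for the other two. If the protocol's own dropout rate is met, the trial is expected to finish below its own minimum.

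What is at stake is mainly the accuracy of the sample-size statement, which any reader can recompute in one line, together with a small part of the planned power.

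**Working it through.** **Inputs.** From section 13: required number 30, dropout 15%, recruited 34, f = 0.473, power 0.80, α = 0.05. From section 17-2: two equal arms. From section 18: two time points, analysed by a mixed ANOVA.

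**1. Can the 30 be reproduced?** Yes, under one assumption that the protocol does not state. Take a repeated-measures ANOVA, between-groups test, with k = 2 groups, m = 2 measurements and correlation ρ between them. The noncentrality is λ = f² · N · m / (1 + (m − 1)ρ), with 1 and N − 2 degrees of freedom. With ρ = 0.5:
- N = 29: λ = 0.473² × 29 × 2 / 1.5 = 8.65, power 0.809. This is the smallest N that reaches 0.80.
- N = 30 (the next even number, for equal arms): λ = 8.95, power 0.823.

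So 30 is a plausible output of that test. For ρ from 0 to 0.8 the same test asks for 20 to 34 participants, so 30 depends on the assumed ρ. The dropout check below does not: it takes the stated 30 as given.

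**2. Does 34 cover 15% dropout from 30?**
- Expected completers: 34 × (1 − 0.15) = 28.9, or 14.45 per arm against 15.
- Losses that 34 can absorb: 34 − 30 = 4, and 4/34 = 11.8%.
- Number needed: 30 / (1 − 0.15) = 35.3. Rounded up to an even number this is 36, which leaves 36 × 0.85 = 30.6.
- Recruiting 35 would leave 35 × 0.85 = 29.75, still under 30.

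**3. Where could 34 come from?** Adding 15% to the required number gives 30 × 1.15 = 34.5. That shortcut is itself too small, because the dropout applies to those recruited and not to those required. Even so it rounds up to 35. The printed 34 follows from 30 only if the shortcut is used and then rounded down.

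**4. What does the shortfall cost in power?** The same test is used, with ρ as an assumption and its range shown:

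| Assumed ρ | 30 completers | 29 completers | 28 completers |
|---|---|---|---|
| 0 | 0.942 | 0.935 | 0.926 |
| 0.5 | 0.823 | 0.809 | 0.794 |
| 0.8 | 0.751 | 0.735 | 0.719 |

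The level of power depends heavily on ρ. The loss does not: going from 30 to 29 costs 0.7 to 1.6 points and from 30 to 28 costs 1.6 to 3.2 points, so about 1 to 3 points overall.

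**The case against.** The best defence is that the slip has almost no consequence. The shortfall is one to two participants. Where ρ = 0.5 reproduces the stated 30, the expected 29 completers still exceed the 0.80 target (0.809), and 28 miss it by 0.006. No design choice or analysis depends on the difference. This stands, and it sets the grade: the point is minor.

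A second defence is that the software may have returned 29, and 29 × 1.15 = 33.35 rounds up to 34. But the protocol states 30 as its minimum, and 29 appears only under an assumed correlation. Even from 29 the proper inflation is 29/0.85 = 34.1, so 35.

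Three stronger readings are tempting, and the document does not support them.
- *A reader might infer that there is no protection against attrition.* There is: four losses are covered. The allowance is overstated, not absent.
- *A reader might infer that the trial is seriously underpowered because of this.* The loss is about 1 to 3 points. Whether 30 was the right starting number for the planned analysis is a separate question, and the dropout arithmetic does not bear on it.
- *A reader might take 0.82 falling to 0.79–0.81 as the protocol's own power figures.* They are not. They rest on a test and a correlation of 0.5 that section 13 does not state, and with ρ between 0 and 0.8 the power at 30 runs from 0.942 to 0.751.

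One could add that, with independent 15% dropout, the chance of keeping at least 30 is 0.41 from 34 recruited. The protocol promises no such probability, and 36 would reach only 0.71, so the comparison of 28.9 with 30 is the fair measure.

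**Conclusion.** The statement is wrong as written, and the error is minor. On section 13's own figures, recruiting 34 at 15% dropout leaves 28.9 expected completers against a minimum of 30. The number matches a dropout rate of 11.8%, and 36 would match 15%. This conclusion uses only the stated 30, 15% and 34, plus equal arms for rounding up to 36. It treats dropouts as lost to the analysis, as the protocol does by recruiting extra participants for them.

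The power cost of about 1 to 3 points rests on the assumed repeated-measures between-groups test and holds for correlations from 0 to 0.8.

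**What to change.** Restate the last sentence of section 13 in one of two ways: 34 participants allow for 11.8% dropout (4 of 34); or, at 15% dropout, about 29 of 34 are expected to complete. In the second case give the power for 29, and name the G*Power test and the correlation used so that the figure can be checked.

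Section 13 speaks of recruitment in the past tense and section 12 dates the study from March 2022 to August 2023, so changing the target is probably no longer possible. If recruitment were still open, 36 is the number consistent with 30 completers and 15% dropout.

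The cost is one sentence and a slightly less favourable stated allowance. Nothing in the design, the analysis or the conduct of the trial changes.

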**14. Inclusion Criteria**

- Age between 20 and 50 years
- Both male and female genders
- Chronic low back pain for more than 6 months, or 3 episodes of low back pain lasting more than one week in the past 12 months
- Unilateral radicular pain secondary to disc herniation at L4/L5 and L5/S1, confirmed by MRI
- Positive result in at least one of the tests: Slump test, Straight Leg Raise, or Lasegue’s sign
- Pain radiation from the anterior posterior calf to the area behind the leg associated with the L4/L5 dermatome to the posterior calf to the heel and outer part of the foot
- Average pain intensity must be 4 or more according to the Numerical Pain Scale
- Average disability score based on the Oswestry Disability Index must be 4 or more
- No spinal tumors
- No cognitive disorders according to Mini Mental Status Examination score ≥ 24
- No spondylolisthesis or spondylolysis
- No structural disorders or spinal deformities such as scoliosis, kyphosis, or severe lordosis
- No spinal fractures
- No brain injuries, including concussions or strokes
- No neurological diseases such as Parkinson’s disease, Alzheimer’s disease, or cerebellar disorders
- No scalp skin lesions or cuts
- No sensory disturbances or loss
- No history of epilepsy
- Not pregnant
- No metallic implants in the brain
- No skin infections
- No pacemakers or other implanted devices
- No visual disturbances
- No depression requiring medication
- No previous spinal surgeries

**15. Exclusion Criteria**

- Participant unwilling to complete or continue the study
- Absence from two consecutive or three non-consecutive treatment sessions
- Participation in a specific exercise program for back pain
- Use of narcotics, sedatives, or analgesics
- Skin irritation or sensitivity in the scalp area during sessions

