**17-2-4. Transcranial Electrical Stimulation**

To apply electrical current, the tDCS device model Neurostim2 from Medina Teb Gostar will be used. Before the patient's arrival, all equipment including electrodes, normal saline, stimulator, cables, elastic bands, and measurement tape will be inspected to ensure they are in good condition and free of defects or damage. The patient will sit on a chair, and the scalp will be examined for any lesions. The researcher will ask the participant to report any skin irritation from the previous session or anything else that would exclude them from the study.

Initially, the electrodes will be placed in sponges soaked with normal saline, and the area of stimulation will be cleaned with alcohol. The electrode size will be 2x4 cm. Stimulation will be applied through two active (anodal) electrodes placed on the scalp. One active electrode will be placed on the M1 region, corresponding to C3 or C4 according to the 10-20 international system. The other active electrode will be placed on the S1 region, which is 2 cm posterior to C3 or C4. Reference (cathodal) electrodes will be placed on the forehead directly above the eyebrow (Figure 6). In general, active electrodes will be placed on the opposite side of the lower back pain, and the reference electrode will be placed on the supraorbital area on the same side as the pain. The device will be set to a current intensity of 1.5 mA for 20 minutes. At the start of stimulation, there will be a 10-second ramp-up period during which the current will gradually increase to 1.5 mA. At the end, there will be a 10-second ramp-down period during which the current will gradually decrease and the device will turn off. Overall, considering the size of the active electrodes, the average current density under these electrodes will be 0.188 mA per square centimeter. The participant will be informed that they might experience a tingling or itching sensation, and the patient will be continuously monitored throughout the treatment. In the sham group, the electrodes will be placed similarly to the intervention group. The device will be turned on, and current will be applied for only 10 seconds, during which the participant will feel a tingling sensation, and then the current will be turned off. The duration of the current application in the sham group will also be 20 minutes (32).

[figure not shown]

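### At least three of the five exclusion criteria in Section 15 act after randomisation and remove patients before the only post-treatment assessment, which can bias the comparison of the arms

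*Protocol*

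**What the plan says.** Baseline eligibility, including the negative conditions (epilepsy, spinal surgery, scalp lesions and so on), sits in Protocol Section 14, Inclusion Criteria. Section 15, Exclusion Criteria, is a separate list of five items:

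- The first is that the patient no longer wishes to go on with the study or finish it.
- The second concerns attendance: "Absence from two consecutive or three non-consecutive treatment sessions".
- The third is that the patient follows some other exercise programme aimed at the back.
- The fourth concerns medication and gives no time point: "Use of narcotics, sedatives, or analgesics".
- The fifth concerns reactions to the stimulation sessions: "Skin irritation or sensitivity in the scalp area during sessions".

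Section 17-2 fixes the time of randomisation: "After the initial assessment, individuals will be randomly assigned to one of two groups". Treatment (12 sessions over 4 weeks) follows. Section 17-2-4 shows exclusion in use during treatment: before stimulation, participants are asked to "report any skin irritation from the previous session or anything else that would exclude them from the study".

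Sections 17 and 17-1 provide two assessments only, one before the first session and one 24 to 48 hours after treatment ends. Section 18 analyses the pre and post values with a two-way mixed ANOVA. Section 13 sizes the trial on pain and allows for loss: "To account for a potential 15% dropout rate, 34 participants were recruited".

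**The concern.** An exclusion criterion is harmless to the comparison when it is checked before randomisation. When it is triggered afterwards, it removes randomised patients, and the two groups that remain need no longer be comparable. That matters if the trigger is related to the arm or to the outcome, and here both are plausible:

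- **Related to arm.** Section 17-2-4 gives the real arm 20 minutes of current and the sham arm 10 seconds, so scalp irritation may occur at different rates. Section 17-2 says that the therapist and evaluator are not blinded, so staff who know the arm apply criteria that need judgement, such as scalp sensitivity.
- **Related to outcome.** Missed sessions, unwillingness to continue and, if the criterion applies on study, analgesic use can depend on how much pain the patient has. Pain is the outcome on which the trial is sized.

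A patient removed part-way has no post-treatment value unless the protocol provides for one, and this protocol does not. The estimated effect of real stimulation could then be too large or too small, depending on which arm loses which patients.

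**Working it through.** **1. Timing of each criterion against randomisation**

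| Section 15 criterion | Can it arise before the first session? |
|---|---|
| Unwilling to complete or continue | In practice no |
| Missed treatment sessions | No |
| Other exercise programme | Not stated; either reading possible |
| Narcotics, sedatives, analgesics | Not stated; either reading possible |
| Scalp irritation during sessions | No |

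So at least three of five act after randomisation. Section 17-2-4 confirms this, since it refers back to the previous session and to exclusion from the study.

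**2. The plan's own figures**

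Inputs from Section 13: f = 0.473, power 0.80, alpha 0.05, N = 30, 15% loss, 34 recruited. A repeated-measures ANOVA (between-groups effect, 2 groups, 2 measurements) has noncentrality N × f² × 2/(1 + rho). With rho = 0.5, which is assumed because the protocol gives none, N = 30 has power 0.823, so the 30 is reproduced. A 15% loss from 34 is 0.15 × 34 = 5.1, or about 5 patients. If loss were purely random, the cost would be in power: with 28 analysed, the same formula gives 0.79.

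**3. One-sided worst case**

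Assumptions: normal scores, 17 per arm (34/2), the k worst patients removed from one arm and none from the other. With p = k/17 and z the upper p quantile of the standard normal, the shift of that arm's mean is phi(z)/(1 − p):

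- k = 1: 0.125 SD
- k = 2: 0.224 SD
- k = 3: 0.315 SD

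Exact finite-sample values are slightly smaller: 0.11, 0.21 and 0.30 SD.

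**4. How the result depends on why patients leave**

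Simulation with no true effect, change-score SD 1, 17 per arm, two-sided t-test and 5,000 runs per scenario. All of these inputs are assumptions. About 30% of one arm is removed (5 of 17):

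| Reason for removal, one arm only | Shift | Type I error |
|---|---|---|
| At random | about 0 | 5.3% |
| Moderately related to outcome | about 0.25 SD | about 10% |
| The five worst outcomes | about 0.46 SD | about 27% |

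The sign reverses when the other arm loses the patients.

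**The case against.** Several objections have force.

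- **Not all five criteria are shown to act on study.** Analgesic or sedative use and other exercise programmes can be read as screening conditions. This stands. A reader might infer that the whole list is post-randomisation, but the text supports that for three items only.
- **A bias is not demonstrated.** A reader might conclude that the comparison is biased. The documents support only that it can be. Random loss gives none, and similar selective loss in both arms would largely cancel.
- **The 0.12 to 0.31 SD is not an expected value.** It is fully one-sided and fully selected on outcome. It is tempting to set 3 of 17 (18%) beside the planned 15% loss, but that 15% is for the whole trial, and 3 of 17 in one arm with none in the other is 3/34 = 8.8% overall. The two are not comparable.
- **Irritation is not shown to come from the current.** Section 17-2-4 mentions tingling or itching, places the electrodes alike in both arms, and describes the alcohol and saline without distinguishing them. It also ends with a 20-minute duration for sham, which fits the 10 seconds of current only if it means time with the electrodes in place. A difference between arms is plausible, not established.
- **The analysis set may be in an SAP.** Section 18 does not say that excluded patients are left out of the analysis, and an SAP that is not shown may define an as-randomised set. A missing analysis-set definition is therefore not the complaint.

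The last objection does not dispose of the point. No SAP can recover an assessment that the protocol caused not to be made, and exclusion from the study with no provision for later assessment is what the protocol fixes.

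**Conclusion.** The point holds in limited form. At least three criteria remove randomised patients from the study before the only post-treatment assessment, and nothing in the protocol keeps them under assessment. The reasons can plausibly be tied to arm or to pain, so the comparison can be biased.

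The documents allow no estimate of size or direction. In a trial of 34, a few selective removals are enough to matter: at worst about 0.12, 0.22 or 0.31 SD for 1, 2 or 3 patients lost from one arm, under the assumptions of normal scores, 17 per arm, and removal of exactly the worst outcomes. If the removals are unrelated to outcome, only power is lost. That the rule exists is certain; that it produces a bias in this trial is not.

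**What to change.** 1. Divide Section 15 into criteria checked before randomisation and events that occur on study (missed sessions, scalp irritation, wish to stop).
2. State for analgesic or sedative use and for other exercise programmes the time point at which the existing criterion applies.
3. State that patients with an on-study event are still invited to the end-of-treatment assessment unless they withdraw consent, and are analysed in the arm to which they were randomised.
4. Keep an analysis of completers as a sensitivity analysis only.
5. Align Section 17-2-4, so that an event during treatment is not described as exclusion from the study.

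Rules on continuing or stopping treatment are left as they are; the change concerns assessment and analysis only.

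Cost: protocol wording and a few extra assessment visits, about five if loss reaches the planned 15% of 34. The downside is some dilution of the estimated effect from patients who did not complete treatment.
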